## **12. Measurements** (This section has been amended. Please refer to the information in “Amendment” section.)

During the study, every effort should be made to keep subjects on the study schedule of procedures (Table 1). These measurements should be performed at baseline and 12, 24, and 36 months. The study window is ranging from -7 to 7 days.

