### 12.5 Uterus Endometrial Thickness Monitoring

We will monitor uterus endometrial thickness using transvaginal ultrasound (Siemens Medical Solutions Systems, Issaquah, WA, USA). Endometrial thickness will be measured at the thickest portion of the endometrium and be included both endometrial layers. The sensitivity of detecting endometrial abnormalities is 92% and for detecting cancer is 96% when an endometrial thickness of 5 mm is used as the upper limit of the normal value (Smith-Bindman and Kerlikowske et al., 1998). During each clinical visit, abnormalities should be evaluated and documented, and follow-up medical care should be provided as needed.

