### 13.3 Adverse Event Collection and Reporting

Any adverse events occurring after the first dose of study medication will be recorded in the subjects’ records and on the CRFs. Information about the occurrence of any adverse events will be sought at all scheduled visits. The investigator is responsible for ensuring that all adverse events observed by the investigator or reported by subjects if SAE occurs. The SAE is reported within 24 hours to the coordinator by completing a Serious Adverse Event Form (Appendix D). In addition, the investigator should ensure that all regulatory requirements are completed.

The following adverse event attributes must be assigned by investigator: diagnosis, signs or syndrome(s) (if known); dates of onset; severity; assessment of relatedness to BSYJF/placebo and action taken. The investigator may be asked to provide follow-up information, discharge summaries, and extracts from medical records or CRFs.

A subject may voluntarily withdraw from treatment due to what she perceives as an intolerable adverse event. If either of these situations arises, the subject

should be strongly encouraged to undergo an end-of-study assessment and be under medical supervision until symptoms cease or the condition becomes stable. Documentation of all such SAEs will be retained in medical records.

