#### 13.4 Safety Monitoring

Monitoring visits will occur on at least 2 occasions in the first year and on at least one occasion each year thereafter. Sites will provide 3-monthly progress reports with information on participant, adverse events, and any protocol deviations. PI will review the reports from the site monitoring visits and the site progress reports every year.

The report will include:

- A list and summarization of adverse events by age and other characteristics
- Whether adverse event rates are consistent with pre-study assumptions;
- Reason for dropouts;
- Whether all participants met entry criteria;
- Whether continuation of the study is justified on the basis that additional data are needed to accomplish the stated aims of the study;
- Conditions whereby the study might be terminated prematurely.

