#### 14. DROPOUT

If any investigator encounters a participant dropout, such as moving away from proximity of the site, incompatible with the intervention (withdrawal), and discontinued the intervention over 3 months. The decision of participant dropout will be reported to the required PI.

Participants will continue to be followed with their permissions if the study intervention is discontinued at the site. These participants will be followed up annually for 36 months for clinical outcomes and adverse events of (1) death from any cause; (2) hospitalization event. We will evaluate compliance by counting the residual at each visit (practical dose/dose application × 100%). Good compliance means the drug actually taken equals 80% to 120 % of the required dosage.

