#### 17.5 Interim Analysis and Stopping Guidelines

An interim analysis will be performed at month 12. Although this is a 3 year study, the primary analysis will occur after all subjects have had the opportunity to complete the month 12 study visit. In order to maintain the blind, study staff at the Office of Scientific Research and Teaching who have direct contact with the sites will have access to results from the interim and primary analyses only at aggregate level until all subjects have completed the study and the treatment assignments have been unblinded. The month 36 data will be analyzed separately at the end of the study.

The study staff at the Office of Scientific Research and Teaching will review the safety and efficacy data for BSYJF/placebo. If at any time there are safety concerns, the study staff will communicate the concerns with a coordinator. The start date will depend on the subject's accrual enrollment.

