### Section: 6.2. Exclusion Criteria

Add:

**For the extension phase, additional exclusion criteria have been defined to protect subjects who have experienced a large bone loss or fragility fracture during the initial 36 month treatment phase of the study.**

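### Section 14 does not name falls, the sole primary endpoint, among the outcomes followed to month 36 in women who stop their capsules

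*Supplement*

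**What the plan says.** **After stopping capsules.** Section 14 (Dropout) lists as dropouts women who move away, women who withdraw, and women who have "discontinued the intervention over 3 months". With their permission they are "followed up annually for 36 months for clinical outcomes and adverse events of (1) death from any cause; (2) hospitalization event". Falls do not appear in the numbered list. Neither amendment lists Section 14 among the parts it changes.

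**Primary endpoint and analysis.** Amendment 1, Section 15.1, makes the number of falls at 36 months the only primary endpoint. The Amendment 2 synopsis analyses all randomized women under ITT, uses LOCF for missing data after baseline in the longitudinal data, compares falls at month 36 by chi-square test, and adds Kaplan–Meier and Cox analyses of time to first fall.

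**Collection of falls.** Amendment 1, Section 12.3, records new falls on a form while the woman is on study and accumulates the count. Section 12 says of its measurements, which include falls: "These measurements should be performed at baseline and 12, 24, and 36 months". Table 1 as updated in Amendment 2 schedules falls at the same visits.

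**Entry to the extension.** Amendment 2, Section 6.2, says that for the untreated extension "additional exclusion criteria have been defined to protect subjects who have experienced a large bone loss or fragility fracture" in the treatment phase. This rule governs entry to the extension and does not bear on falls recording after capsules stop.

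**Planning figures.** Section 11 assumes 19% falls incidence on placebo, an annual 50% reduction on BSYJF, and 20% drop-out from 70 women per group.

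**The concern.** An ITT comparison of falls at month 36 needs fall information to month 36 from every randomized woman who can still be reached, whether or not she takes capsules. Section 14 is the only place that says what is collected once capsules stop. Its list was written when falls were one of four primary endpoints, and it was not revised when they became the only one. A site that follows the list literally would ask about death and hospital admission at the annual contact and put the falls form away.

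Carrying an accumulated fall count forward then enters the unobserved months as months without a fall. The Kaplan–Meier and Cox analyses would instead censor these women when recording stops, which assumes that stopping is unrelated to the risk of falling. Neither approach replaces the missing data. If stopping is similar in both groups, the main cost is events and power. If it differs, the group that stops more often will appear to fall less.

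**Working it through.** **The plan's drop-out figure.** Section 11 inflates 55 per group for 20% drop-out: 55 / (1 − 0.20) = 68.75, so 69; the plan recruits 70. The allowance is reproduced to within one woman. Over 140 women it is 140 × 0.20 = 28, or 14 per group. Whether 55 suits the falls endpoint is a separate matter.

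**Expected first-time fallers with full follow-up.** Assumption: the Section 11 rates are annual and constant, 19% on placebo and 19% × 0.5 = 9.5% on BSYJF.
- Placebo, 36 months: 1 − 0.81³ = 46.9%; 70 × 0.469 = 32.8.
- BSYJF, 36 months: 1 − 0.905³ = 25.9%; 70 × 0.259 = 18.1.
- Total: 50.9.

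**First-time fallers missed if falls recording ends when capsules stop.** Assumption: all 28 stop at one common month. Missed per group = 14 × (36-month risk − risk up to stopping). Totals are from unrounded figures.

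| Stopping month (assumed) | Risk up to stopping, placebo / BSYJF | Missed, placebo | Missed, BSYJF | Total | Share of 50.9 |
|---|---|---|---|---|---|
| 12 | 19.0% / 9.5% | 14 × (0.469 − 0.190) = 3.9 | 14 × (0.259 − 0.095) = 2.3 | 6.2 | 12.2% |
| 18 | 27.1% / 13.9% | 14 × (0.469 − 0.271) = 2.8 | 14 × (0.259 − 0.139) = 1.7 | 4.4 | 8.7% |
| 24 | 34.4% / 18.1% | 14 × (0.469 − 0.344) = 1.7 | 14 × (0.259 − 0.181) = 1.1 | 2.8 | 5.6% |

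Each total is an upper bound for its stopping month, because some of the 28 could not be followed under any wording.

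**Effect on the comparison when stopping is equal.** Let 20% of each group stop uniformly over 36 months, with later falls counted as none. With h = −ln(1 − annual risk), the observed risk among stoppers is 1 − (1 − e^(−3h)) / (3h).
- Placebo: 25.9% among stoppers; overall 0.8 × 46.9% + 0.2 × 25.9% = 42.7%.
- BSYJF: 13.6% among stoppers; overall 0.8 × 25.9% + 0.2 × 13.6% = 23.4%.
- The risk ratio barely moves (0.552 to 0.549). Two-sided 5% power at 70 per group falls from about 74% to about 68%.

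**Effect when stopping is unequal.** Assume no drug effect, with both groups at the placebo rate. The false difference is the difference in stopping proportions × (46.9% − 25.9%).
- 10% versus 30%: 0.20 × 21.0 points = 4.2 points.
- 15% versus 25%: 0.10 × 21.0 points = 2.1 points.

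The plan does not predict unequal stopping; these splits are illustrations.

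**The case against.** The best answer is that the plan intends to collect these falls. The falls schedule exempts nobody who stopped. Amendment 2, Section 5.1, makes an untreated 10-year phase part of the study, so being on study is not the same as being on capsules, and participants are asked to record every fall in that phase. Section 14 does say that women who stop continue to be followed, and its reference to clinical outcomes could include falls. The consent form was removed from the text and the procedures manual is not shown; either might settle the matter.

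This rules out the stronger reading, which a reader might infer, that falls after stopping will certainly go uncollected. It does not remove the ambiguity. The numbered list names two events and the primary endpoint is not one of them. The explicit instruction to keep recording falls is given for the extension, not for women who stop during treatment. Section 13.3 encourages an end-of-study assessment after withdrawal for an adverse event, but that does not secure falls to month 36.

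It is also fair that the arithmetic overstates what the fix would recover. Some dropouts will have moved away or refused contact, the stopping months are assumed, and first-time fallers stand in for the number of falls.

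A second inference is tempting: because the bone-loss rule applies only at entry to the extension, women with a large loss at month 12 or 24 are unprotected. The documents do not support it. DXA measures the loss directly at those visits. The falls form records fractures, and Section 12.3 obtains a confirming radiograph. General routes also exist: "Information about the occurrence of any adverse events will be sought at all scheduled visits"; "Sites will provide 3-monthly progress reports with information on participant, adverse events, and any protocol deviations"; "If at any time there are safety concerns, the study staff will communicate the concerns with a coordinator". Nothing bars a clinician from acting on a scan. The extension criteria are said to be already defined, so they may stand in a document not shown. Wanting a named trigger would be a preference, not a fault in the plan.

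**Conclusion.** The point holds as an ambiguity with a cheap remedy. Section 14, read literally, leaves the sole primary endpoint out of follow-up after capsules stop, which does not fit an ITT analysis to month 36. At the Section 11 rates and 20% drop-out, about 3 to 6 of about 51 first-time fallers (6% to 12%) would be missed at most, for assumed stopping at month 24 back to month 12; stopping before month 12 would raise this. With equal stopping the loss is mainly power, about 6 percentage points under uniform stopping. With unequal stopping a false difference of roughly 2 to 4 points is possible in the illustrations above. The documents do not show that stopping will differ, so bias is a risk and not a finding. No conclusion about bone safety during treatment follows. Priority is low to moderate.

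**What to change.** Amend Section 14 to say that women who stop capsules for any reason stay, with their permission, in falls recording to month 36, on the same form and at the same annual contacts, in addition to death and hospitalization. It would help to add to Section 12.3 that on study means from randomization to month 36, whether or not capsules are being taken.

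The cost is one or two sentences by amendment, plus falls forms for up to about 28 women off capsules. The form and the annual contact already exist. No change to the BMD assessments at months 12 and 24 is needed for this point.

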### Section: 9. Drug Administration

Add:

**All the included participants will be asked to record every number of fall during 10 years extension follow-up.**

Section: 15.2 Secondary Endpoints

Add:

**Additional endpoint:**

**Number of falls at the end of 10 years extension follow-up will be performed by chi-square test.**

Section: 17.2 Diet and Exercise Control

Add:

During the entire trial, the subjects will be advised to follow the guideline for daily dietary intake and physical activities, such as intaking high-protein diet, avoiding alcohol abuse and smoking, and keeping active in daily physical activities. The questionnaire for daily dietary intake and physical activities should be recorded at 12, 24, 36 months during 36-month clinical trial **and at the 3rd, 6th and 10th year during 10-year follow-up.** Calcium and vitamin D supplement on their own should be prohibited in 36-month clinical trial.

## Section: 12. Table 1 Schedule of Assessments (updated)

| Assessment                       | Screening | Baseline | Treatment |           |           | Follow-up           |                     |                      |
|----------------------------------|-----------|----------|-----------|-----------|-----------|---------------------|---------------------|----------------------|
|                                  | Wk. -2-0  | Wk.0     | Mo.
12 | Mo.
24 | Mo.
36 | Yr. 3 rd | Yr. 6 th | Yr. 10 th |
| General information              |           |          |           |           |           |                     |                     |                      |
| Informed consent                 | √         |          |           |           |           |                     |                     |                      |
| Medical/Medication history       | √         |          |           |           |           |                     |                     |                      |
| Physical exam (Height & Weight)  | √         |          | √         | √         | √         |                     |                     |                      |
| BMD screening                    | √         |          |           |           |           |                     |                     |                      |
| Observations                     |           |          |           |           |           |                     |                     |                      |
| Falls                            |           | √        | √         | √         | √         | √                   | √                   | √                    |
| BMD and lean mass                |           | √        | √         | √         | √         |                     |                     |                      |
| TUG test                         |           | √        | √         | √         | √         |                     |                     |                      |
| Bone biomarkers                  |           | √        | √         | √         | √         |                     |                     |                      |
| Hematology                       |           | √        | √         | √         | √         |                     |                     |                      |
| ECG                              |           | √        | √         | √         | √         |                     |                     |                      |
| B-ultrasound                     |           | √        | √         | √         | √         |                     |                     |                      |
| DDIPA                            |           | √        | √         | √         | √         | √                   | √                   | √                    |
| Adverse events                   |           |          | √         | √         | √         |                     |                     |                      |
| Others                           |           |          |           |           |           |                     |                     |                      |
| Drug dispensing                  |           | √        | √         | √         |           |                     |                     |                      |
| Drug return                      |           |          | √         | √         | √         |                     |                     |                      |
| Combined disease and Medications | √         |          | √         | √         | √         |                     |                     |                      |

### **Rationale and Changes (Original Protocol 1.1 to Version 1.2):**

To assess the latent effects of BSYJF interventions on number of falls in late postmenopausal women, eligible subjects will enter a 10 year extension phase at the end of the initial 36 months treatment phase. Some changes were updated to be aligned with the trial.
